**Methods:**

Non-inferiority RCT with internal pilot, health economic evaluation and qualitative communication sub-study. The study is conducted in England, Northern Ireland, Scotland and Wales at both specialist children’s hospitals and district general hospitals. Children (aged 4–15 years inclusive) diagnosed with acute uncomplicated appendicitis that would normally be treated with an appendicectomy are eligible for the RCT. Exclusion criteria include clinical/radiological suspicion of perforated appendicitis, appendix mass or previous non-operative treatment of appendicitis. Sample size is 376 participants, recruited by surgeons and supported by research staff and randomised with a 1:1 allocation ratio to either non-operative treatment pathway (intervention) or appendicectomy (control). Participants in the intervention arm are treated with antibiotics, analgesia and regular clinical assessment to ensure clinical improvement. Participants in the control arm receive appendicectomy. Randomisation is minimised by age, sex, duration of symptoms and centre. The primary end-point is a composite outcome of treatment success at 1 year following randomisation. Secondary outcomes include: duration of hospital stay, measures of recovery from acute appendicitis, complications, need for further treatment, persistent symptoms, health care resource use, quality of life and costs. Adverse events, serious adverse events and suspected unexpected serious adverse events are collected directly on the database and by paper form up to 12-month visit. Primary outcome will be analysed on a non-inferiority basis using a 20% non-inferiority margin to test the hypothesis that non-operative treatment pathway is non-inferior to appendicectomy. Children and families who are approached for the RCT will be invited to participate in the embedded qualitative sub-study. This will include recording of recruitment consultations, which will inform future interventions to optimise recruitment. We have involved children, young people and parents in study design and delivery.

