### Participant timeline {13}

Table 4 shows the participant timeline for patient’s observations and procedures.

**Table 4 Tab4:** Schedule of observations and procedures

**Visit/time point (all measured from randomisation:**	**Baseline/randomisation**	**Treatment**	**Dis-charge**	**1 week**^**a**^ (+ 3 days)	**2 weeks**^**a**^ (+ 3 days)	**3 weeks**^**a**^ (+ 3 days)	**4 weeks**^**a**^ (+ 3 days)	**6 weeks** (− 1 week/+ 2 weeks)	**4 months**^**a**^ (− 1 week/+ 2 weeks)	**8 months**^**a**^ (− 1 week/+ 2 weeks)	**12 months**^**a**^ (− 1 week/+ 2 weeks)
Informed consent	**X**										
Eligibility evaluation	**X**										
Medical history	**X**										
Diagnostic tests as per standard practice (blood test—Total WBC/CRP/Neutrophil, CT scan, Ultrasound)	**X**										
Pregnancy test^b^	**X**										
Physical exam (abdomen exam)								**X**			
Vital signs (temperature)	**X**										
Randomisation	**X**										
Appendicectomy (arm B only)		**X**									
IV antibiotics (arm A only)		**X**									
Doctor/healthcare professional assessment	**X**							**X**			
Histology following surgery								**X**	**X**	**X**	**X**
Discharge assessment			**X**								
Adverse Events	**X**		**X**	**X**	**X**	**X**	**X**	**X**	**X**	**X**	**X**
Health economics—resource use	**X**		**X**	**X**	**X**	**X**	**X**	**X**	**X**	**X**	**X**
CHU-9D	**X**			**X**	**X**	**X**	**X**	**X**	**X**	**X**	**X**
Patient data collected on app				**X**	**X**	**X**	**X**				
Client service receipt inventory (CSRI)								**X**	**X**	**X**	**X**
Recurrence								**X**	**X**	**X**	**X**
Complication requiring intervention under general anaesthesia	**x**							**x**	**x**	**x**	**x**

^a^To be collected remotely via phone call and/or app

Data collected on app:

▪ Pain relief taken Y/N

▪ CHU 9D proxy and self-report where appropriate

▪ Antibiotics taken Y/N

▪ Able to do normal daily activities Y/N

▪ Attended school Y/N

▪ Able to do full activities Y/N

▪ Parents missed work Y/N

▪ The last week have you had any contact with a health care professional(s) for your child’s appendicitis? Y/N

^b^Only for those of childbearing potential

NB: The Participant/legal representative is free to withdraw consent at any time without providing a reason. When withdrawn, the participant will continue to receive standard clinical care. Follow up data will continue to be collected (unless the participant/legal representative has specifically stated that they do not want this to happen)

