### Sample size {14}

We will test the hypothesis that non-operative treatment pathway is non-inferior to appendicectomy. We anticipate a difference between the treatment arms with respect to the primary outcome of 8 percentage points (assuming 88% treatment success in the appendicectomy group and 80% in the non-operative group). Since there are potential further benefits to non-operative treatment that are not included within the primary outcome (e.g. greater parental acceptability, avoidance of general anaesthesia, avoidance of surgical complications, cost), it is appropriate to use a wider non-inferiority margin for our analysis. The size of this non-inferiority margin was explored with both surgeons and parents in our feasibility study [5, 13–19], which was pre-specified at 20% for this trial. Of interest, this is the same margin that was defined by a Cochrane review as being ‘clinically relevant’ [31].

Given that the assumed difference in success rate is non-zero (8%), a one-sided 5% significance level was deemed appropriate. Based on the estimates of non-zero assumed difference of 8% and non-inferiority margin of 20%, with a one-sided 5% significance level and 90% power, this trial will require a total of 318 cases analysed at 1 year (159 per arm). Allowing for 15% loss to follow up, the recruitment target will be 376 participants (188 per arm).

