## Statistical methods

### Statistical methods for primary and secondary outcomes {20a}

The analysis of the primary outcome (treatment success at 1 year) will be based on an intention-to-treat (ITT) population, which includes all children who have been randomised to a treatment arm (non-operative treatment pathway or appendicectomy), regardless of compliance or treatment received, and have completed data for the outcome and timepoint being analysed. Primary analysis will be by a mixed effects logistic regression model controlling for the minimisation factors with age, sex and onset of pain duration as fixed effects, each with two levels, and study site (10 or more levels) as a random effect. It is possible that controlling for study site will not be possible due to stability of the statistical model and this will be explored. Analysis will produce the absolute risk difference between the two treatment arms with a one-sided 95% confidence interval applying bootstrapping, which can then be assessed against the pre-specified non-inferiority margin of 20%. The number and percentage of children meeting the definition of treatment success at 1 year following randomisation will also be presented.

Individual outcomes that contribute to the composite primary outcome will be presented solely as descriptive statistics within the treatment pathway to which they apply (e.g. recurrent appendicitis is not relevant to the appendicectomy treatment arm). Secondary outcomes that apply to both treatment pathways will be analysed in superiority comparisons between the treatment pathways in ITT analyses, with the exception of adverse events (AEs) for which only descriptive statistics will be provided.

Further details of this, and methods for analysis of secondary outcomes, will be documented in a Statistical Analysis Plan. All analyses will be performed using STATA 19 [33].

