We acknowledge that Svensson and colleagues [10] have undertaken a small pilot RCT comparing these two treatments, and recently, since the initiation of this trial, two other groups [36, 37] have published findings of larger RCTs (one in Australia, one multinational). Additionally, Minneci and colleagues [11] have reported a large series of children with uncomplicated appendicitis from the USA (*n* = 1068) of whom 370 were treated non-operatively. Using a propensity score matched analysis, they assessed the impact of treatment approach on outcomes, but they did not use randomisation to assign patients to treatment arms. The two larger trials [36, 37], with a similar non-inferiority randomised design to this study, concluded that non-operative treatment was inferior to appendicectomy based on a non-inferiority margin of 20%. Despite this, we believe there is benefit in further comparative effectiveness research in this field for a number of reasons. Firstly, there are subtle differences between our protocol and others—the use of the complicated appendicitis score and a minimum of 24 h of non-operative treatment may both independently increase the likelihood of success of non-operative treatment. Secondly, we believe a further RCT is justified that is specific to the UK setting to provide an assessment of these healthcare technologies in the UK. This is particularly true for a comparative health economic analysis, since the NHS is a unique healthcare economic environment. We also note some differences in the management of appendicitis in the UK compared to other countries that reinforce the rationale for a trial within the UK. Most notably, in the UK, there is only limited use of diagnostic radiology, a relatively high negative appendicectomy rate and limited use of same day discharge after appendicectomy. Since all these factors may influence the comparative effectiveness and cost effectiveness of treatment, we believe a further RCT in the UK is justified. Finally, we note that, although analysis of the primary outcome is important, there is also significant value in understanding the impact of different management strategies on many of the secondary outcomes, since these data are likely to inform shared decision-making models with families going forwards. Understanding these accurately in the UK healthcare setting will result in the most value for NHS patients in the future.

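### The primary model is valid, but it leaves out the complicated appendicitis score collected before randomisation, which could add a little precision

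*Protocol article*

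**What the plan says.** All references are to the Protocol article.

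- **Statistical methods {20a}** names the covariates of the primary model: "age, sex and onset of pain duration as fixed effects, each with two levels", plus study site as a random effect that may be dropped if the model is unstable. The output is an absolute risk difference with a bootstrapped one-sided 95% confidence interval, read against the 20-point margin. Further detail is left to a statistical analysis plan that is not shown.
- **Sequence generation {16a}** minimises on the same four factors: age (4–8 or 9–15 years), sex, symptom duration (cut at 48 h) and centre. The complicated appendicitis score is neither a minimisation factor nor a model covariate.
- **Eligibility criteria {10}** exclude a child who scores 4 or more. Table 2 builds the score from rebound tenderness, pain of 48 h or longer and temperature (1 point each), and neutrophil count and CRP (2 points each).
- **Participant timeline {13}**, Table 4, places the blood tests at baseline, under "Diagnostic tests as per standard practice (blood test".
- **Discussion** lists "the use of the complicated appendicitis score" among the differences from other trials that may raise the success of non-operative treatment.
- **Sample size {14}** works from two unadjusted proportions, "assuming 88% treatment success in the appendicectomy group and 80% in the non-operative group", "with a one-sided 5% significance level and 90% power", and makes no allowance for covariate adjustment.

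**The concern.** The score must be settled before a child can be randomised, so it is a baseline severity measure that the trial already holds. Severity is a plausible predictor of failed or recurrent non-operative treatment. A model that uses a prognostic baseline variable usually estimates the risk difference somewhat more precisely, and it removes the part of the estimate that is due to chance imbalance in that variable. The planned model uses one of the five score items, pain duration. The other four, which include the two heaviest-weighted, enter neither the minimisation nor the analysis. What is at stake is a small amount of precision around a difference that will be compared with a fixed margin.

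**Working it through.** **1. The plan's own figure.** Inputs from Sample size {14}: success 88% and 80%, "non-inferiority margin of 20" points, one-sided 5%, 90% power; allocation is 1:1.

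- Variance sum = 0.88×0.12 + 0.80×0.20 = 0.1056 + 0.1600 = 0.2656.
- Distance from the assumed difference to the margin = 0.20 − 0.08 = 0.12.
- n per arm = 0.2656 × (1.645 + 1.282)² / 0.12² = 158, against the stated 159.
- Recruitment: 159/0.85 = 187.1, rounded up to 188 per arm, or 376 in total.
- At 159 per arm, SE = √(0.2656/159) = 0.0409, and power = Φ(0.12/0.0409 − 1.645) = 90.2%.

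The plan's figure is reproduced.

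**2. What adding the score could gain.** The article gives no effect of the score on outcome, so this step is assumption. For a covariate-standardised risk difference in large samples, with success probabilities pc and pt at each score value,

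n × variance = E[pc(1−pc)] + E[pt(1−pt)] + Var(pt−pc)/2.

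*Worked example.* Scores 0 to 3 are equally common, there is no effect in the appendicectomy arm, and the odds of failure double per point in the non-operative arm. Then pc = 0.88 throughout and pt = 0.93, 0.87, 0.77, 0.63.

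- E[pc(1−pc)] = 0.1056.
- E[pt(1−pt)] = (0.0651 + 0.1131 + 0.1771 + 0.2331)/4 = 0.1471.
- Var(pt−pc)/2 = (0.0193 − 0.0064)/2 = 0.0065.
- Total = 0.2592, which is 2.4% below 0.2656 (2.5% without rounding). Power becomes 90.8%.

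The ranges below cover three assumed distributions of scores 0/1/2/3: 25/25/25/25%, 30/30/25/15% and 10/20/35/35%.

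| Assumed odds ratio for failure per point | Variance reduction | Power at 159 per arm |
|---|---|---|
| 1.3 to 1.5, both arms | 0.8–2.6% | 90.4–90.8% |
| 2.0, both arms | 4.4–6.9% | 91.3–91.9% |
| 1.5 to 2.0, non-operative arm only | 0.6–2.5% | 90.3–90.8% |
| 1.5, opposite directions by arm | 0.2% or less | 90.2% |

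These ignore the overlap with pain duration, so they overstate the extra gain. A simulation with pain duration balanced and adjusted for, again under an assumed score distribution, gave a change from about −0.5% (a slight loss, when the score has no effect or opposite effects by arm) to about +5% (odds ratio 2.5 per point non-operative, 1.5 control). A 5% cut gives SE = √(0.2656×0.95/159) = 0.0398 and power of 91.4%.

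**3. Chance imbalance.** For an imbalance in mean score of 0.2 SD or more, z = 0.2/√(2/159) = 1.78, so the two-sided probability is about 7.5%. In the worked example the slope is −0.10 per point in the non-operative arm and 0 in the other, averaging −0.05. With SD 1.118, the shift is 0.05 × 0.2 × 1.118 = 1.1 points. Across all scenarios it runs from about 0.1 to 1.9 points. The largest is 1.9/4.09 = 0.46 of a standard error, against a 12-point distance to the margin.

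**4. Load on the model.** Expected failures = 159×0.20 + 159×0.12 = 31.8 + 19.1, about 51. The planned model has four fixed coefficients besides the intercept (arm, age, sex, pain duration). A linear score makes five, or about 51/5 = 10 failures per coefficient.

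**The case against.** The strongest case against is that nothing here is wrong. Adjusting for every minimisation factor matches the analysis to the design, and leaving out a further baseline covariate under randomisation causes no average bias and no inflation of type I error. That stands in full.

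Three stronger readings are tempting, and the article does not support them.

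- *Severity is controlled by neither design nor analysis.* Pain of 48 h or longer is both minimised on and adjusted for. Eligibility also truncates the score to 0–3, so a child with both raised neutrophils and raised CRP (2 + 2 = 4) cannot enter.
- *The Discussion shows that the sponsor regards the score as prognostic.* That text concerns selecting children by the score, compared with other trials' protocols. It does not say that a 0 differs from a 3 among enrolled children.
- *A severity imbalance would pass uncorrected into the result.* Given an adverse 2-point shift, the chance of meeting the margin would be Φ(10/4.09 − 1.645) = Φ(0.80), about 79%. But such draws are uncommon, favourable ones are equally likely, and the confidence interval and the 90% power already average over both.

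The direction of effect is also uncertain. Negative appendicectomy counts as failure, so low scores might mean more failure after surgery while high scores mean more failure without it. The gain would then vanish.

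Availability for every child is an inference: blood tests follow standard practice, and Table 2 does not say how a missing item is scored. The unseen analysis plan may already hold a severity-adjusted sensitivity analysis. The protocol does, however, name the primary model's covariates itself, so the suggestion about that model remains open.

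**Conclusion.** The point holds as an optional improvement. The planned primary model is valid; it does not use four of the five items of a score that the trial must establish before randomisation. Adding the score would change the variance of the risk difference by about 0 to 5%, lifting power from about 90% to at most about 92%, and by nothing if its effects oppose each other in the two arms. This rests on assumed odds ratios and score distributions. The 92% comes from the most favourable scenario, which ignores overlap with pain duration.

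A reader might infer a flaw that threatens the non-inferiority conclusion, or a model made unsound by two-level covariates. Neither follows. Sex is naturally binary, site is a random effect, and the two-level age and pain-duration terms mirror the minimisation; banding age costs at most some precision.

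**What to change.** Before any outcome data by arm are seen, prespecify the following:

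- Add the score as a fixed effect in the primary model, without its pain-duration point, because pain duration is already a covariate. (With a single linear term and the same 48 h value in both places, the fitted model is the same either way; leaving the point out keeps the coefficient interpretable.)
- Enter age as continuous. Keep sex, pain duration and site as planned.
- Obtain the risk difference by standardising over the covariates, with the planned bootstrap interval.
- State how a missing score item is handled.
- Keep the minimisation-factor-only model as a sensitivity analysis, and as the fallback if the larger model is unstable.

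The cost is wording in the analysis plan and one or two more degrees of freedom with about 51 expected failures. No new data are needed, since the score is required to confirm eligibility. If the score proves to have no effect, the expected loss of precision is negligible (about 0.5% of variance in the simulation above).

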### Interim analyses {21b}

No interim analyses are planned for this trial. Internal pilot data will be analysed after 12 months from the start of site set-up to assess trial and recruitment progress. Number of sites (i) in set-up and (ii) open to recruitment will be assessed. Overall recruitment and within-site recruitment will be assessed.

### Methods for additional analyses (e.g. subgroup analyses) {20b}

Sub-group analyses exploring study recruitment and outcomes in specialist paediatric centre versus DGH recruiting sites will be conducted. Subgroup analysis exploring outcomes from laparoscopic versus open procedures was considered but given the likely lack of open procedures may not be possible or meaningful.

#### Health economic analysis

Overall, the economic evaluation will report the long-term results from the CEA at 1 year using the primary outcome, reporting cost per successfully treated child. The CUA will report the short to medium-term cost per QALY gained at 6 weeks, when full recovery for both arms is expected. Extending the time to 1 year risks diluting the actual difference between the two treatment arms in QALY terms, and it is important to show the short-term implication in QALY terms. However, sensitivity analysis will explore long-term implications by incorporating recurrence of appendicitis, both in terms of increased costs and reduced QALYS. The potential of bias will also be explored using sensitivity analysis if increased cross-over between arms is observed. As part of the economic analysis, we will also report the economic implications for the NHS in terms of defining tariff for the non-operative treatment option and reporting on the economic impact this might have to the NHS. We will develop a full Health Economics Analysis Plan.

### Methods in analysis to handle protocol non-adherence and any statistical methods to handle missing data {20c}

The primary analysis will compare the overall ‘non-operative treatment pathway’ versus ‘appendicectomy’ and will take into account whether the initial non-operative approach was successful or not by designating per-protocol treatment switches to appendicectomy as treatment failure. This analysis, based on a comparison of two treatment pathways rather than non-operative treatment versus appendicectomy, reflects the proposed clinical pathway under investigation. It also accounts for treatment switches due to non-operative treatment failure by designating these as a treatment failure at 1 year (the primary outcome). If the non-operative treatment pathway is inferior to appendicectomy, this will be reflected in the numbers of patients who switch to appendicectomy and this will be reflected in the analysis proposed.

The per-protocol analysis will be a secondary analysis to explore the effect of non-adherence to allocated treatment (which are most likely to be due to parents’, children’s or clinicians’ desire to revert to either appendicectomy or non-operative treatment ahead of the trial schedule).

Missing data patterns will be explored to investigate mechanisms of missingness. We will consider the impact of any missing data on the primary outcome, such as sensitivity analyses.

### Plans to give access to the full protocol, participant level-data and statistical code {31c}

Southampton Clinical Trials Unit (SCTU) is committed to the responsible sharing of clinical study data and samples with the wider research community. Data and sample access is administered through the SCTU Data and Sample Release Committee, who will consider requests once the final analysis has been published. All data and appropriate documentation will be stored for a minimum of 10 years after the completion of the trial.

## Oversight and monitoring

### Composition of the coordinating centre and trial steering committee {5d}

SCTU provides day-to-day organisational support for the trial along with the Chief Investigator. A Trial Management Group (TMG) comprised of the core trial team and all co-applicants meet once per month. An independent TSC meets at least once a year. The role of the TSC is to provide oversight for the trial and advice on all aspects of the trial through its independent Chair to the TMG, Sponsor, Funder and SCTU.

### Composition of the data monitoring committee, its role and reporting structure {21a}

The Data Monitoring Committee (DMC) meets at least once a year and its role is to safeguard the interests of trial participants, monitor the main outcome measures including safety and efficacy and monitor the overall conduct of the trial. The DMC will receive and review information on the progress and data relating to this trial and provide advice on the conduct of the trial to the TSC. The DMC will inform the Chair of the TSC if, in their view, the results are likely to convince a broad range of clinicians, including those supporting the trial and the general clinical community, that, on balance, one trial arm is clearly indicated or contraindicated for all participants or a particular category of participants, and there is a reasonable expectation that this new evidence would materially influence participant management. The DMC finalised its reporting structure at its first meeting on 8-Dec-2022 and agreed a charter.

